### Intervention

Both groups will receive acupuncture treatment once a day for 5 days a week (excluding Saturday and Sunday) and the trial medication (DS/placebo capsule) three times a day for seven consecutive days. Treatment will be administered by Korean medicine physicians with 6 years of formal university training in Korean medicine, a licence to administer treatment, and at least 1 year of clinical experience. To ensure strict adherence to the study protocol, the physicians will receive training together and employ the same techniques.

#### Acupuncture treatment

All participants will receive acupuncture at the ST36, ST41, BL60, BL62, KI3, KI6, GB39, and GB40 points on the affected side [25]. Only sterile, stainless steel, disposable acupuncture needles (size, 0.25 × 30 mm; Dong Bang Acupuncture, Inc., Boryeong, Republic of Korea; product no. A84010.02) with guide tubes will be used. The depth of insertion will be 10–20 mm depending on the location of the needle [34]. After insertion, the needles will be left in position for 15 min in every session. Manual stimulation and electroacupuncture will not be applied (see Table 2).

**Table 2 Tab2:** Revised STandards for Reporting Intervention in Clinical Trials of Acupuncture (STRICTA)

	Item criteria	Description
1.Acupuncture rationale	1a. Style of acupuncture	Korean Medicine Therapy
	1b. Reasoning for treatment provided – based on historical context, literature sources, and/or consensus methods, with references where appropriate	1. Discussion among four physicians who practice Korean medicine (consensus) 2. Textbook of acupuncture and moxibustion medicine 3. Relevant articles [20] Selection of treatment regions based on textbooks, related papers, and expert discussions
	1c. Extent to which treatment varied	Standardized treatment
2. Details of needling	2a. Number of needle insertions per subject per session (mean and range where relevant)	8
	2b. Names (or location if no standard name) of points used (uni-/bilateral)	ST36, ST41, BL60, BL62, KI3, KI6, GB39, GB40
	2c. Depth of insertion, based on a specified unit of measurement or on a particular tissue level	The depth of insertion is 10 to 20 mm, depending on the location of the needle [21]
	2d. Responses sought	No *de qi* or muscle twitching – only sensation due to needle insertion
	2e. Needle stimulation	None
	2f. Needle retention time	15 min per session
	2 g. Needle type	sterile, stainless, disposable acupuncture needles (size 0.25 × 30mm; Dong Bang Acupuncture, Inc., Boryeong, Republic of Korea; product no: A 84010.02)
3. Treatment regimen	3a. Number of treatment sessions	5
	3b. Frequency and duration of treatment sessions	Five times/week for 1 week, 15 min per session
4. Other treatment components	4a. Details of other interventions administered to the acupuncture group	None
	4b. Setting and context of treatment – including instructions to practitioners – as well as information and explanations given to patients	Practitioner-patient conversation about the context of the treatment, life habits, and daily life management
5. Practitioner background	5a. Description of participating acupuncturists	Korean medicine physician with the following qualifications: 6 years of formal university training in Korean medicine, a license, and at least 1 year of clinical experience
6. Control or comparator interventions	6a. Rationale for the control or comparator in the context of the research question, with sources that justify the choice	Korea Institute of Oriental Medicine. Ankle sprain Korean Medicine Clinical Practice Guideline. Seoul: Elsevier Korea. L.C.C. 2015;163–7
	6b. Precise description of the control or comparator; details for items 1–3 above with the use of sham acupuncture or any other type of acupuncture-like control	Acupuncture combined with a Kinesiotape (AcuKT) group will receive the ankle meridian tendino-musculature and figure-of-eight-shaped form of KT treatment after acupuncture treatment by same practitioner. The KT treatment method will be conducted as follows: first, an I-shaped tape will be applied from ST42 to ST36 over the tibialis anterior muscle. Second, an I-shaped tape will be applied from GB42 to GB34 over the peroneus longus and brevis muscles. Third, an I-shaped tape will be applied from the abductor digiti minimi muscle and wrapped around the ankle in a figure-of-eight shape to the abductor hallucis muscle covering both the medial and lateral malleoli

#### Trial medication

The trial medications will include DS and placebo capsules, which will be identical in appearance, taste, and smell. The DS formulation composed of granular extracts of nine herbal substances, will be a gray-brown powder contained in a 0.6-g pink capsule (Fig. 2). The placebo will be composed of 300 mg of corn starch, 150 mg of lactose hydrate, 1.5 mg of magnesium stearate, and 48.5 mg of caramel colorant. Both medications will be administered at a dose of three capsules three times daily (total daily dose, nine capsules) for a period of 1 week.

**Fig. 2 Fig2:**
[figure not shown]
Appearance of *Dangguixu-san* (DS) and placebo capsules used in the study

The manufacturing process for the DS capsules is as follows. First, 0.63 g of *Angelicae gigantics radix*, 0.42 g of *Paeoniae radix rubra*, 0.42 g of *Linderae radix*, 0.42 g of *Cyperi rhizoma*, 0.42 g of *Sappan lignum*, 0.33 g of *Carthami flos*, 0.29 g of *Persicae semen*, 0.25 g of *Cinnamomum cassia*, and 0.21 g of *Glycyrrhizae radix* are added to the extractor. The mixture is extracted with 8–10 volumes of purified water at 80–100 °C for 3–4 h. The extract is filtered (100 mesh), concentrated under reduced pressure at ≤ 60 °C, and dried to obtain 350 mg of a granular extract. Then, 45 mg of lactose hydrate, 100 mg of corn starch, and 5 mg of magnesium stearate are mixed into the granular extract, and the mixture is converted into granules, dried, crushed, and filled into capsules.

Capsules will be sourced from Kyungjin Pharmaceutical Co., Ltd. (Icheon, Gyeonggi-do, Republic of Korea (product no. 02190)). The medication will be dispensed as 0.6-g capsules packed in sealed boxes containing a 1-week dose.

Between the preintervention period and 4 weeks after treatment completion, participants will not be allowed to take the following drugs: NSAIDS, pain relievers, steroids, or adherent inflammatory pain relievers; drugs containing potassium, licorice, glycyrrhizic acid, furosemide, ethacrynic acid, or trichloromethazine; and drugs containing any of the main ingredients of DS. Participants will be asked to return their medication boxes to allow enumeration of leftover capsules and for monitoring participant adherence.

### Outcome measurements

VAS, FAOS, edema, and EQ-5D-5 L scores will be assessed before, at the end of, and at 4 weeks after treatment completion. EQ-5D-5 L scores will be additionally recorded at 26 weeks after treatment completion. The number of recurrent ankle sprains will be recorded at 4, 8, 12, and 26 weeks after treatment completion.

#### Primary outcome

Because the objective of this study is to investigate the efficacy of DS therapy for pain relief in patients with ALAS, changes in the pain severity (measured using VAS) will be considered as the primary outcome. The VAS will be a 10-cm straight line marked at each end with the anchor labels “no pain” and “pain as bad as it could be” [35]. Patients will be asked to mark the line at a point representing their severity of pain. Scores will be recorded in millimeters, with a total score range of 0–100 mm [36].

#### Secondary outcomes

Secondary outcomes will include changes in FAOS, edema, EQ-5D-5 L scores, and the number of recurrent ankle sprains. The FAOS is a self-administered questionnaire specific to feet and ankles. It is designed to assess week-to-week changes in symptoms and function after foot and ankle injuries and comprises five subscales: pain (nine items), other symptoms (seven items), activities of daily living (17 items), sports and recreational activities (five items), and foot-and-ankle-related quality of life (four items). The subscales are scored separately using a Likert response format, with higher scores indicating higher levels of function [37].

Edema will be measured in centimeters using the figure-of-eight method. A measurement tape will be applied across the following landmarks in a figure-of-eight fashion: navicular tuberosity, distal tip of the lateral malleolus, distal tip of the medial malleolus, and base of the fifth metatarsal. The resulting value will be compared with the corresponding value for the healthy ankle [38].

The European Quality of Life Five-Dimension Scale (EQ-5D) is a generic instrument for assessment of health-related quality of life. It is based on a descriptive system that defines health in terms of five dimensions: mobility, self-care, usual activities, pain/discomfort, and anxiety/depression. Each dimension has three response categories: no, some, or extreme problems. The EQ-5D-5 L, which will be used in this study, is a new version of the EQ-5D that includes five levels of severity in each of the existing five EQ-5D dimensions [39].

Recurrent ankle sprain will be defined as ankle sprain occurring as a result of participation in sports or other daily activities and causing one or more of the following: discontinuation of the sports activity, inability to fully participate in the next planned sports activity, inability to go to work/school the following day, and the requirement of medical attention (ranging from onsite care administered by a general practitioner to personal care administered by a sports physician) [40].

### Incidence of adverse events

AEs are undesirable and unintentional signs, symptoms, or diseases that appear during or after treatment in a clinical trial. The participants in this study will be required to voluntarily report any AEs. All AEs that occur during the trial will be documented. Adverse events that might occur in this study include skin irritation, urticaria, itching, anorexia, stomach discomfort, diarrhea, nausea, vomiting, pseudoaldosteronism, and hypokalemia. The CRC will record all AEs in detail, including the time and date of occurrence, degree of severity, any measures related to the treatment of the AE, and any potentially causal relationship between the treatment and the AE, and report all AEs to the PI and relevant IRB. In case of serious AEs (SAEs), defined as those causing severe disability or malfunction, appropriate measures will be taken and the incident will be immediately reported to the PI and relevant IRB. In case an AE occurs because of the clinical trial, participants will notify the CRC and PI and will be compensated by the “Clinical Trial Compensation.”

### Quality assurance

This protocol has been reviewed and revised several times by experts on acupuncture, herbal medicine, orthopedics, statistics, and methodology. Before the trial, all researchers will be requested to attend a series of training sessions, which will ensure that the personnel involved fully understand the trial protocol and standard operating procedures (SOPs) that will be employed during the study. The Data Monitoring Committee will be composed of the PI and CRC. The clinical trial will be monitored by a clinical research associate (CRA), who will check all documents related to the clinical trial, including Case Report Forms (CRFs) and SOPs, and ensure that the clinical trial is conducted in accordance with the prescribed protocols and SOPs. Monitoring will be conducted independent of the PI. In the event that the protocol described herein is revised, the revisions will require approval from the Ministry of Food and Drug Safety and the IRB of Semyung University Korean Medicine Hospital in Chungju.

### Sample size estimation

Because of the lack of adequate preliminary studies, we adopted a pilot study design with 24 participants in each group, considering the limited research funds, study period, and recruitment opportunities.

### Statistical analysis

Baseline characteristics will be compared between the two groups. Repeated measures analysis of covariance (RM ANCOVA) will be performed to determine differences between groups, considering the different baseline characteristics (covariance). Continuous data will be presented as means and standard deviations and compared using the independent *t* test or Wilcoxon’s rank sum test, while categorical data will be presented as frequencies and percentages and compared using the chi-square or Fisher’s exact test. VAS scores for pain and the secondary outcomes (FAOS, edema, and EQ-5D-5 L scores) will be evaluated by RM ANCOVA. Dependent variables will include values measured before, at the end of, and at 4 weeks after treatment completion. Changes in the VAS score from baseline to treatment completion (visit 5) and 4 weeks after treatment completion (visit 6) will be determined by the paired *t* test. A repeated contrast test will be performed to account for time differences in each group. A *P* value of < 0.05 will be considered statistically significant. We will perform per-protocol analysis for the assessment of efficacy and a supplementary full analysis set. All statistical analyses will be performed using SPSS version 22.0 (SPSS Inc., Chicago, IL, USA).

Data for subjects who meet the dropout criteria (*i.e.*, < 80% compliance with the protocol, incidence of SAEs, reluctance to continue the trial, incomplete data that could influence the trial, large error in protocol or significant deviation in implementation, and decision to terminate trial participation by the PI or IRB) will be excluded. Missing values will be implemented by multiple imputations. In addition, differences between subjects who complete the study and dropouts will be statistically analyzed to determine whether any particular factor is significantly associated with participation dropout. Interim analyses will not be performed.

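### The RM ANCOVA names no covariates and appears to choose them from observed baseline imbalance, so adjustment for baseline VAS is not guaranteed

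*Protocol article*

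**What the plan says.** All of the relevant wording is in the Protocol article, mostly under Statistical analysis.

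- The section opens with "Baseline characteristics will be compared between the two groups". The next sentence introduces RM ANCOVA "to determine differences between groups, considering the different baseline characteristics (covariance").
- Continuous data are to be "compared using the independent *t* test or Wilcoxon’s rank sum test"; categorical data get chi-square or Fisher's exact tests.
- On the model for the outcomes: "VAS scores for pain and the secondary outcomes (FAOS, edema, and EQ-5D-5 L scores) will be evaluated by RM ANCOVA".
- On the responses in that model: "Dependent variables will include values measured before, at the end of, and at 4 weeks after treatment completion".
- Under Primary outcome, "changes in the pain severity (measured using VAS) will be considered as the primary outcome".
- The significance criterion is "A *P* value of < 0.05 will be considered statistically significant"; sidedness is not stated.

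No covariate is named anywhere in the article, and Randomization and blinding names no stratification factor. Under Sample size estimation, "we adopted a pilot study design with 24 participants in each group, considering the limited research funds, study period, and recruitment opportunities"; no effect size, SD, correlation or power is given.

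**The concern.** Read together, the two opening sentences of Statistical analysis make adjustment depend on which baseline characteristics turn out to differ. In a randomised trial those differences arise by chance. How far a variable happens to differ between arms says nothing about how strongly it predicts later pain, and the strength of prediction is what makes a covariate worth having. Such a rule can pass over baseline VAS, which is likely to be among the best predictors of later VAS, and bring in variables that are irrelevant to pain.

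Two things are at stake: precision, in a trial of 24 per arm that has little to spare, and a primary model that is known before the data are seen.

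**Working it through.** There is no planned power figure to reproduce, because the sample size rests on feasibility. The check has four steps.

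**1. What decides the covariates.** If a difference means P<0.05 (an inference, since no threshold is stated), the chance that at least one of k independent baseline variables is flagged under perfect randomisation is 1 − 0.95^k. This gives 5% for k = 1, 23% for k = 5, 34% for k = 8 and 40% for k = 10. Baseline VAS itself would be flagged in about 5% of trials.

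**2. Where baseline VAS sits.** It is listed among the responses and is not named as a covariate. With the baseline value as a response, the treatment effect can be read from a group-by-time contrast, which acts like a change score, or from a group main effect averaged over all three time points.

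**3. Change contrast against fixed adjustment, baseline to visit 5.** From the article: n = 24 per arm and alpha 0.05. Assumed: two-sided test, effect 15 mm, SD 22 mm at each visit, correlation r between visits.

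- SD of change = 22 × √(2(1 − r)).
- Residual SD after adjustment for baseline = 22 × √(1 − r²).
- Noncentrality = (15 / SD) × √(24/2); power from the noncentral t (46 df for change, 45 df for adjustment).

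| r | Change SD | Noncentrality | Power | Adjusted SD | Noncentrality | Power | Loss (points) |
|---|---|---|---|---|---|---|---|
| 0.3 | 26.03 | 2.00 | 49.8% | 20.99 | 2.48 | 67.8% | 18 |
| 0.5 | 22.00 | 2.36 | 63.8% | 19.05 | 2.73 | 76.1% | 12 |
| 0.7 | 17.04 | 3.05 | 84.7% | 15.71 | 3.31 | 89.9% | 5 |

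The adjusted figures ignore the small cost of chance baseline imbalance. A simulation of always adjusting gave 67%, 75% and 90%.

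**4. Main effect and type I error.** These come from a separate simulation: 24 per arm, 10,000 trials per setting, equal correlation between the three time points, an assumed effect of 0.8 SD at both post-baseline visits, and the mean of those visits as target. Power at r = 0.3, 0.5 and 0.7 was:

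- baseline always a covariate: 95%, 97% and 99%;
- change from baseline: 75%, 88% and 98%;
- group main effect over all three time points: 69%, 60% and 52%.

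The main effect loses most because it averages in a time point at which treatment cannot yet have acted. With no treatment effect, adjusting for baseline only when it differed at P<0.05 rejected in 5.0%, 3.9% and 3.2% of trials, against 5.0%, 4.8% and 5.2% when always adjusting.

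**The case against.** The strongest objection is that baseline VAS is never absent from the analysis: it is a response in the repeated-measures model, and the primary outcome is defined as a change. That is correct, and a reader who infers that baseline pain would usually be ignored goes too far. It also rules out a larger loss that a reader might compute. Comparing visit 5 scores with no use of baseline has power of 64% at every correlation (15/22 × √12 = 2.36), 26 points below fixed adjustment at r = 0.7. The plan does not specify that analysis. What remains is that a change contrast is still less efficient than adjustment at each correlation examined.

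Second, the wording is loose. The phrase could mean the various baseline characteristics, and a baseline comparison is an ordinary entry in a results table. A P<0.05 entry rule is nowhere stated. Selection on observed difference remains the likelier reading, and a missing threshold leaves more room for choice, not less.

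Third, a reader might infer that a data-dependent model inflates false positives. The simulation shows no inflation; the selection rule is slightly conservative at the higher correlations. Rates of 7.0% to 8.5% arise only if the analyst picks the better of the adjusted and unadjusted results after seeing both, which the article does not propose.

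Fourth, this is a declared pilot, and a full covariate list is commonly left to an analysis plan. That would answer a mere omission. Here the article appears to state a selection rule, which an analysis plan following it would inherit. It also sets a superiority hypothesis and a significance criterion, so the efficiency of the primary test matters.

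**Conclusion.** The point stands as one of efficiency and pre-specification. The article names no covariate and appears to let observed baseline differences choose them. The primary model is therefore not fixed in advance, and adjustment for baseline VAS is not assured. Against a change-type contrast at visit 5, the loss is about 18, 12 and 5 power points at correlations 0.3, 0.5 and 0.7; a group main effect that includes baseline would lose more on a like-for-like comparison. These sizes rest on an assumed effect, SD and correlations, none of which the documents give. The documents do not support a claim that type I error is inflated, that baseline VAS is missing from the model, or that a P<0.05 entry rule is laid down.

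**What to change.** Replace the covariate wording under Statistical analysis with a fixed rule:

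- The baseline value of the outcome being analysed is always a covariate, whatever the observed balance.
- The responses are the post-baseline values only (visits 5 and 6). This is needed because adding baseline VAS as a covariate while keeping it as a response would put it on both sides of the model.
- Covariates are not selected from baseline comparisons.
- Any model with further covariates is a sensitivity analysis.

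Sprain grade may be added as a pre-specified covariate, since it is determined at eligibility, but this is optional: the documents do not show that it predicts VAS.

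The cost is one sentence and about one degree of freedom. No new data are needed, because Table 1 already schedules VAS, FAOS, edema and EQ-5D-5L at visit 1.

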### Randomization and blinding

After the acquisition of written informed consent and completion of baseline measurements, the 48 enrolled participants will be assigned serial numbers generated using a randomization tool (http://www.randomization.com) and randomly allocated to one of the two study groups (*n* = 24 each). The serial number codes will be inserted into opaque envelopes that will be sealed and stored in a double-locked cabinet.

Blinding will be achieved by randomized labeling and prepackaging of DS and placebo capsules, which will be identical in appearance, taste, and smell. The DS and placebo capsules provided by the pharmaceutical company will be labeled with numbers in accordance with the randomization schedule. Investigators will administer these medications in accordance with the randomization number. Randomization and uncovering will be performed by a third-party team of statisticians. Thus, participants, investigators, and outcome assessors will remain blinded to treatment allocation until study completion.

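### The between-group RM ANCOVA counts the pre-randomisation score as an outcome and names no efficacy term; read as a group main effect, it reports two thirds of the mean post-treatment difference

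*Protocol article*

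**What the plan says.** All of the following is in the protocol article.

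- **Purpose of the model** (Statistical analysis): "Repeated measures analysis of covariance (RM ANCOVA) will be performed to determine differences between groups". The covariates are described only as baseline characteristics that differ; baseline VAS is not named among them.
- **Outcomes covered** (Statistical analysis): "VAS scores for pain and the secondary outcomes (FAOS, edema, and EQ-5D-5 L scores) will be evaluated by RM ANCOVA".
- **Dependent values** (Statistical analysis): "Dependent variables will include values measured before, at the end of, and at 4 weeks after treatment completion".
- **Other VAS analyses** (Statistical analysis): changes from baseline to visit 5 and to visit 6 "will be determined by the paired *t* test", which is a within-group test. For the time contrasts: "A repeated contrast test will be performed to account for time differences in each group".
- **Order of baseline and allocation** (Randomization and blinding): "After the acquisition of written informed consent and completion of baseline measurements, the 48 enrolled participants will be assigned serial numbers".
- **Primary outcome** (Primary outcome): "changes in the pain severity (measured using VAS) will be considered as the primary outcome". No primary visit is named.

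**The concern.** RM ANCOVA is the only between-group analysis that the text assigns to VAS by name. Its default between-subjects output is the group effect averaged over all dependent values. One of the three is measured before allocation, when treatment cannot have acted. That value contributes no signal. Unless baseline is also adjusted for, it does contribute noise.

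The size of the estimate is at stake for the primary outcome and three secondary outcomes, and possibly power too. Size matters here because the Sample size estimation and Discussion sections present the trial as a pilot that should form a basis for further research.

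**Working it through.** The plan states no effect size, SD, correlation or power, so there is no figure of its own to reproduce.

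**Inputs from the article:** 24 per arm; dependent values at baseline, visit 5 (end of treatment) and visit 6 (4 weeks later); significance level 0.05, taken as two-sided.

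**Assumed inputs:** SD 22 mm at every visit; equal correlation r = 0.5 between visits (0.3 and 0.7 as a range); true effects d5 and d6 as in the tables.

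**1. Size of the estimate.** The group main effect over three visits has expectation (0 + d5 + d6)/3. The mean post-treatment effect is (d5 + d6)/2. The ratio is 2/3 whatever the SD, the correlation or the effects.

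| d5, d6 (mm) | Three-visit group effect | Mean of visits 5 and 6 | Ratio |
|---|---|---|---|
| 15, 5 | 20/3 = 6.7 | 10.0 | 2/3 |
| 15, 0 | 15/3 = 5.0 | 7.5 | 2/3 |
| 15, 15 | 30/3 = 10.0 | 15.0 | 2/3 |

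**2. Standard errors at r = 0.5.** For a per-patient SD s, the standard error of the group difference is s × √(2/24).

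- Three-visit mean, baseline not a covariate: variance 22² × (1 + 2r)/3 = 484 × 0.667 = 322.7; s = 17.96; SE = 5.19 mm.
- Mean of visits 5 and 6, adjusted for baseline: variance 22² × [(1 + r)/2 − r²] = 484 × 0.50 = 242; s = 15.56; SE = 4.49 mm.
- Three-visit mean with baseline also a covariate: the baseline value is then fully explained, so estimate and SE are both two thirds of the previous line; SE = 2.99 mm.

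**3. Power** (noncentral t; 46 and 45 degrees of freedom).

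| d5, d6 (mm) | Three-visit, baseline not a covariate | Baseline-adjusted mean of visits 5 and 6 |
|---|---|---|
| 15, 5 | 6.67/5.19 = 1.29 → 24% | 10/4.49 = 2.23 → 59% |
| 15, 0 | 5/5.19 = 0.96 → 16% | 7.5/4.49 = 1.67 → 37% |
| 15, 15 | 10/5.19 = 1.93 → 47% | 15/4.49 = 3.34 → 90% |

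At r = 0.3 the two columns are 29%, 18%, 56% against 54%, 34%, 87%. At r = 0.7 they are 21%, 14%, 41% against 73%, 49%, 97%. With baseline as a covariate in the three-visit model, the test statistic and power equal those of the right-hand column; only the estimate stays shrunk.

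**4. The group-by-time reading.** This term compares changes between groups, so nothing is averaged with baseline. Its power (F test on 2 and 92 degrees of freedom, r = 0.5) is about 55%, 67% and 67%. A single change-from-baseline contrast at visit 5 has SD 22 × √(2(1 − r)) = 22 mm, SE 6.35 mm and power 64%. The baseline-adjusted visit 5 difference has SD 22 × √(1 − r²) = 19.05 mm, SE 5.50 mm and power 76%.

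**The case against.** The strongest reply is that a layout with baseline among the repeated values is legitimate when the group-by-time term is read. The primary outcome is defined as change in pain, which suits that term. The choice of term could sit in a fuller document that is not shown. This stands in part: the text does not say that the main effect is the test, so the dilution is conditional. But the article does fix the dependent values, and it words both the paired test and the repeated contrast as within-group. The only between-group reading it offers is left open to the diluted one.

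Second, baseline VAS may be among the unlisted covariates. If so, power is kept. The estimate is still two thirds of its size.

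Third, continuous data are also to be summarised as means and SDs, so a later trial might recover an undiluted difference. That softens the consequence. It does not correct the estimate from the planned model.

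A reader might also infer two stronger things. One is that including baseline shrinks the effect by more than a third. It does not: in the (15, 0) case, averaging visits 5 and 6 alone already takes 15 mm to 7.5 mm, and only the step from 7.5 to 5.0 mm is due to baseline. The other is that the loss should be measured against about 76% power at visit 5. The protocol names no primary visit, and that comparison mixes the baseline problem with the inclusion of visit 6. The like-for-like comparator is the baseline-adjusted mean of both visits. On that comparator the group-by-time test is not always weaker: in the (15, 0) case it has 67% against 37%.

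**Conclusion.** The defect is real but conditional, and the wording should be corrected before the data are analysed. If the group main effect is the efficacy result, the DS-placebo difference is expected to be two thirds of the mean post-treatment difference for each of the four outcomes. This needs no assumption beyond randomisation after baseline. If that shrunken difference were used with a post-treatment SD to size a later trial, the sample size would be inflated by (3/2)² = 2.25.

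The power loss needs a further condition, that baseline VAS is not a covariate. Its size (24%, 16%, 47% against 59%, 37%, 90%) rests on the assumed SD, correlation and effects. If the group-by-time term is intended, there is no dilution. The documents do not establish which reading is meant, so it cannot be said that the reported result will be too small, only that the plan as worded allows it.

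**What to change.** Preferred: replace the sentence on dependent variables. Use the visit 5 and visit 6 scores only, with the baseline score of the same outcome as covariate and terms for group, visit and group-by-visit. Report the baseline-adjusted group difference at each visit with its 95% CI, for VAS, FAOS, edema and EQ-5D-5L. Reporting by visit also keeps an effect that fades by visit 6 from being hidden in an average.

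Minimum: keep the three-value layout and state that efficacy is judged by the between-group contrast in change from baseline (group-by-time) at a named visit. This removes the dilution but is less precise than adjustment: at visit 5 under the assumptions above, SE 6.35 against 5.50 mm.

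Either change is a sentence or two of text. It uses data already scheduled for collection, and the planned software can fit it.
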